# Effect of acupotomy in knee osteoarthritis patients: study protocol for a randomized controlled trial

**DOI:** 10.1186/s13063-021-05247-z

**Published:** 2021-04-20

**Keywords:** Acupotomy, Needle-knife, Knee osteoarthritis, Study protocol, Randomized controlled trial

## Abstract

**Background:**

Symptomatic knee osteoarthritis (KOA) is common in China. Pharmacological therapy is not the first recommendation because of its safety issues. Nonpharmacological therapy, such as lifestyle adjustments, weight loss, muscle strengthening, and aerobic exercise programs, is strongly recommended for KOA. However, these approaches may fail due to poor patient compliance. There is a lack of high-quality randomized controlled trials of acupotomy, an effective treatment for KOA. This study was designed to investigate the efficacy of acupotomy in patients with KOA.

**Methods:**

A total of 136 patients will be enrolled at the First Affiliated Hospital of Guangzhou University of Chinese Medicine and assigned to the acupotomy group or sham acupotomy group according to the block randomization scheme. Patients in the acupotomy group will receive 2 sessions of acupotomy for 2 weeks (once a week). Patients in the sham group will receive 2 sessions of sham stimulation for 2 weeks (once a week). All patients will use indomethacin cream externally. The primary outcome will be the Western Ontario and McMaster Universities Osteoarthritis Index (WOMAC), and the secondary outcomes will be the visual analog scale (VAS) score, plantar pressure distribution test result, X-ray examination findings, musculoskeletal ultrasound findings, maximum knee circumference, joint mobility, and quality of life. Measurements will be taken at baseline, 1 week after the end of treatment, and at the 3- and 6-month follow-ups.

**Discussion:**

To the best of our knowledge, this will be the first single-blind, sham-controlled study of acupotomy. The outcome assessors will also be blinded. The aim of this work is to demonstrate the efficacy of acupotomy in treating KOA.

**Trial registration:**

Chinese Clinical Trial Registry ChiCTR2000033047. Registered on 18 May 2020.

**Supplementary Information:**

The online version contains supplementary material available at 10.1186/s13063-021-05247-z.

## Background

As the 11th highest contributor to global disability, knee osteoarthritis (KOA) causes social and familiar burdens [1]. In China, symptomatic KOA is common [2]. Symptomatic KOA causes pain and impaired knee function. A total of 3.9% of KOA patients suffer from severe symptoms, which lead to disability [3]. Pharmacological therapy is not recommended because of its limited efficacy and associated safety issues [4]. Nonpharmacological therapy has been used extensively in treating KOA [5]. For instance, lifestyle adjustments, weight loss, muscle strengthening, and aerobic exercise programs are the recommended methods for first-line treatment [6]. In a systematic review, tai chi was reported to be beneficial in terms of the Western Ontario and McMaster Universities Osteoarthritis Index (WOMAC) (total SMD = -0.41) and in terms of stiffness (total SMD = − 0.20) [7]. However, patient compliance plays an important role in these treatments. At 9 months after stopping exercise, the benefit of exercise in patients with KOA was lost [8]. Thus, we are seeking an effective nonpharmacological therapy with better patient compliance to treat KOA.

Acupotomy is a special type of acutherapy. Unlike standard acupuncture, acupotomy involves a needle-knife with a thicker diameter and flat needle. This needle-knife can enter deep tissues to loosen adhesions. In clinical practice, acupotomy has been mainly used for the treatment of bone diseases and diseases causing chronic soft tissue injury. Acupotomy can alter the balance of mechanical forces around joints, restore the normal state of joint stress, and alleviate inflammation [9, 10]. Therefore, it has a good effect on KOA, frozen shoulder, tennis elbow, and heel pain [11–13]. Acupotomy has been used to treat KOA for more than 30 years [14]. Although previous studies [15–17] have demonstrated the efficacy of acupotomy, it is currently unclear whether acupotomy is an effective treatment for KOA due to a lack of high-quality trials. Therefore, we designed a randomized, single-blind, sham-controlled trial to explore the efficacy of acupotomy in treating KOA.

## Methods

### Study design

Based on the Declaration of Helsinki, we designed a parallel, block-randomized, single-blind, sham-controlled trial. The study protocol has been reported in accordance with the Standard Protocol Items: Recommendations for Clinical Interventional Trials (SPIRIT) guidelines [18] (Additional file 1). This study will be performed at the First Affiliated Hospital of Guangzhou University of Chinese Medicine from June 2020 to June 2023 (Fig. 1).

**Fig. 1 Fig1:**
[figure not shown]
Flowchart of the study design

### Participants and recruitment

Participants will be recruited by posting bulletin board advertisements and contacting community doctors. The recruitment information will mainly include eligibility criteria and contact details. A well-trained investigator in the acupuncture department will be responsible for the recruitment of participants. Patients meeting the eligibility criteria will be invited to the clinical research center for further examinations (e.g., X-ray examination, musculoskeletal ultrasound examination, plantar pressure distribution testing and blood analysis), which will be completed within 1 day.

### Inclusion criteria

Findings meeting the radiological diagnostic criteria for level I, II, or III KOA based on the Kellgren-Lawrence classification [19];A visual analog scale (VAS) pain score above 4 points in the past month;Age from 40 to 70 years;No use of other related treatment drugs or related treatment methods within 2 weeks;Informed consent.

### Exclusion criteria

Pregnancy, lactation, or a plan for pregnancy during the trial;Infectious or serious diseases, such as those affecting the cardiovascular, cerebrovascular, liver, kidney, or hematopoietic systems;Local infection, ulceration, vascular nerve damage, or deep abscess in the knee joint;History of severe knee trauma or surgery or arthroscopy;Other diseases that cause knee pain, such as tumors, knee joint tuberculosis, rheumatoid arthritis, and gouty arthritis;Use of oral corticosteroids or administration of an intra-articular knee injection within 1 month or participation in another clinical trial within 3 months;Allergy to the medical devices involved in this trial;Contraindications to the use of indomethacin plaster, as follows: history of allergy to indomethacin, liver or kidney dysfunction (alanine aminotransferase (ALT) and aspartate aminotransferase (AST) levels more than 2 times the normal value and blood creatinine (Cr) level more than the normal value); asthma, urticaria, or allergic reactions after taking aspirin or other nonsteroidal anti-inflammatory drugs; history of gastrointestinal bleeding or perforation after anti-inflammatory drug use; active gastrointestinal ulcer bleeding, previous recurrent ulcer bleeding; and severe heart failure or history of perioperative coronary artery bypass surgery, etc.;Bleeding tendency, such as long-term use of warfarin, aspirin, and other anticoagulants;History of sedative hypnotic, opioid analgesic, or alcohol abuse;Inability to cooperate with relevant experiments and measurements.

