#### Sham acupotomy group

Patients assigned to the sham acupotomy group will receive mock acupotomy, which is performed similar to real acupotomy, but without manual stimulation to achieve any real effect. The needle-knife will pierce through the skin only and remain under the skin for 10 s to simulate the manipulation time. Patients will receive 2 sessions of sham acupotomy for 2 weeks (once a week).

Clinicians would give patients indomethacin cream (import drug registration number: H20181060, Nipro Pharma Corporation Saitama Site Plant 2) if the acupotomy treatment is not effective. All patients could receive up to one time of indomethacin cream per day. They can only receive indomethacin cream at most twelve times during the study. The researchers will record the use of indomethacin every day.

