### Safety monitoring

To protect the rights and interests of patients, all patients will be informed of the potential benefits and risks of the trial before they enroll. After confirming that the patient understands the relevant content, we will ask the patient to sign an informed consent form. Patients who do not sign the informed consent form will not be admitted to the study.

Acupotomy may trigger adverse events, including dizziness and local hematoma. If dizziness occurs during treatment, the doctor will stop the treatment immediately. Then, the doctor will lay the patient down on the pillow and provide warm water. If hematoma occurs, the patient will be instructed to apply a local cold compress and switch to a hot compress after 24 h to promote dissipation and absorption of the blood. If an adverse drug reaction occurs, the drug will be discontinued. Active clinical observation and symptomatic treatment will be carried out.

The Ethics Committee of the First Affiliated Hospital of Guangzhou University of Chinese Medicine will monitor the safety of this trial and provide advice (e.g., endpoint adjustment) if necessary. When an adverse event occurs in a patient, the researchers will record the details, such as the time, severity, duration, treatment measures, and event outcomes. The responsible doctor will determine the causal relationship between the treatment method and the adverse event and decide whether the patient will be allowed to continue the study. Relevant information will be reported to the ethics committee on the same day.

The following are the criteria for terminating a patient from the study: (1) the patient has experienced a serious adverse event, the patient has requested to suspend participation in the trial, or the trial operator believes that it is necessary for the patient to be terminated from the trial; (2) during the study, the patient is found to have a systemic disease that could not be detected before the start of the clinical trial; (3) for other reasons, the researchers believe that the patient is not suitable for continued treatment; and (4) the patient has privately received other interventions that may affect the outcomes.

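### The indomethacin exclusion names liver or kidney dysfunction, but its laboratory limits are joined by 'and', so the literal rule would not exclude either one alone (minor wording error)

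*Protocol article*

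**What the plan says.** The Exclusion criteria section of the protocol article has one item for contraindications to indomethacin. It opens with "history of allergy to indomethacin, liver or kidney dysfunction" and defines the dysfunction in a bracket. Term and bracket together run "liver or kidney dysfunction (alanine aminotransferase (ALT) and aspartate aminotransferase (AST) levels more than 2 times the normal value and blood creatinine (Cr) level", and the creatinine limit is then given as above normal. The liver part of the bracket is "alanine aminotransferase (ALT) and aspartate aminotransferase (AST) levels more than 2 times the normal value". The kidney part follows after a second 'and'. The same item ends with "and severe heart failure or history of perioperative coronary artery bypass surgery", followed by an open-ended 'etc.'.

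A separate exclusion covers "Infectious or serious diseases, such as those affecting the cardiovascular, cerebrovascular, liver, kidney, or hematopoietic systems". It gives no laboratory limit.

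The Abstract has all patients using the cream. The text under Sham acupotomy group has clinicians giving it when the treatment is not effective, up to once a day for any patient, and adds: "They can only receive indomethacin cream at most twelve times during the study". Under Safety monitoring: "If an adverse drug reaction occurs, the drug will be discontinued". The Participants and recruitment section lists a blood analysis among the further examinations for patients who meet the eligibility criteria.

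**The concern.** The bracket gives the test that screening staff would apply to a laboratory report, and its connective differs from that of the term it explains. Taken at its word, the bracket requires the liver limit and the kidney limit to be exceeded together. Dysfunction of one organ would then not exclude, although the term says that it should.

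At stake is a safety screen for a non-steroidal anti-inflammatory drug that any participant may be given. A patient with an isolated raised creatinine is the plainest case: contraindicated by the term, admitted by the literal bracket. A second, lesser question is whether ALT and AST must both be above the limit or whether one is enough.

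**Working it through.** The plan states no figure on this point, so there is none to reproduce. The check sets the term beside the bracket.

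**Inputs**, all from the Exclusion criteria section:
- Connective in the term: liver *or* kidney.
- Liver limit: ALT *and* AST more than 2 times normal.
- Connective between the organs in the bracket: *and*.
- Kidney limit: creatinine above normal.

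**Three ways to apply the bracket:**
- A, word for word: ALT and AST and creatinine.
- B, organ by organ with both transaminases required: (ALT and AST) or creatinine.
- C, organ by organ with either transaminase enough: ALT or AST or creatinine.

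| Values above their limit | What the term implies | A | B | C |
|---|---|---|---|---|
| None | eligible | eligible | eligible | eligible |
| All three | excluded | excluded | excluded | excluded |
| Creatinine only | excluded | **eligible** | excluded | excluded |
| Creatinine and one transaminase | excluded | **eligible** | excluded | excluded |
| ALT and AST, creatinine normal | excluded | **eligible** | excluded | excluded |
| One transaminase only | not settled | eligible | eligible | excluded |

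**Reading the table.**
1. Reading A contradicts the term in the three rows in bold. In each of them the liver limit or the kidney limit is met on its own, which the term makes sufficient. Readings B and C agree with the term wherever the term gives an answer.
2. The last row differs in kind. The term does not say how many transaminases make up liver dysfunction, so B and C are both compatible with it. This is an ambiguity, not a contradiction.
3. The surrounding text supports the organ-by-organ intent. In the same item, 'and' introduces the last of several conditions that each exclude alone ("and severe heart failure or history of perioperative coronary artery bypass surgery"). The bleeding-tendency item does the same with "long-term use of warfarin, aspirin, and other anticoagulants", where nobody would require every drug at once.
4. That list-style 'and' also leans towards reading C for the transaminases, but the document does not say so.
5. No other section gives laboratory limits that would correct the bracket.

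**The case against.** The strongest reply is that no clinician would read the bracket as a joint requirement. It explains a two-part term by giving the limit for each part, and in such a gloss 'and' merely joins two definitions. The section uses 'and' in this list style elsewhere, and the 'or' in the term tells the reader how to apply the bracket. Much of this stands: it is why the intent can be called fairly clear and why the point is minor. It does not make the wording right. The same item also writes 'or' where alternatives are meant, so a screener cannot tell from usage alone that the 'and' in the bracket means 'or'.

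A second reply is that the article condenses a fuller protocol, which may settle the matter. For the liver-kidney connective this does not help, because the article states the rule and its limits itself and the defect is in what it states. For ALT and AST the reply has more force, which is one reason to treat that part as a clarification only.

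A third reply points to the backstops: the separate exclusion for serious liver or kidney disease, the open-ended list, the cap of twelve uses of a cream, and withdrawal of the drug after an adverse reaction. These do limit the harm. However, the serious-disease item sets no laboratory limit and so does not clearly catch an isolated abnormal value, and stopping the drug acts only after exposure.

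A reader might go further, count combinations of test results, and infer that the criterion fails to catch most of the patients it should. The documents do not support this. Such a count rests on the literal reading that the term itself argues against. Combinations are also not patients: they are not equally frequent, and no frequencies are given. Nor does anything in the article show that screening staff would apply the joint requirement.

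**Conclusion.** The literal rule conflicts with the term it defines. Word for word, it would not exclude raised creatinine alone, or raised transaminases with normal creatinine. The term makes the organ-by-organ intent fairly clear, so this is a minor wording error in an operative safety criterion and worth correcting because the drug is open to every participant. It has no effect on sample size, error rates or analysis.

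Whether one raised transaminase is enough is an open detail alongside this error and should not be presented as a second contradiction.

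The number of patients affected is unknown. The conclusion assumes that the bracket is the rule used at screening and that the screening blood analysis supplies the three values. The article does not list the tests in that analysis.

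**What to change.** Change the 'and' before creatinine to 'or'. This alone removes the conflict with the term.

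In the same line, write 'ALT or AST', so that one raised transaminase is enough. This is the safer reading. If the sponsor does intend to require both transaminases, keep 'ALT and AST' and make only the first change.

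The line would then read: *ALT or AST more than 2 times the normal value, or creatinine above the normal value*. The screening form should carry the same rule. Replacing 'normal value' with 'upper limit of normal' would be tidier, but it is optional and not part of the defect.

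The cost is one line in the criterion and one at screening, using only values that the criterion already names, with no added test or visit. The 'either transaminase' wording may produce a few more screen failures.

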### Intervention

#### Acupotomy group

The patients will be placed in a supine position with the knees flexed 30 ~ 45°. A cushion will be placed beneath the knees. The physicians will select 6 points from a point set, as follows. The point set contains 8 points, including the upper and lower points of the medial collateral ligament of the affected knee joint, the upper and lower points of the lateral collateral ligament, the subpatellar ligament points, the upper point of the patella, the muscle insertion point of the popliteal muscle, and the medial popliteal fossa stimulation points. We will stimulate 6 points for unilateral knee pain and 12 points for bilateral knee pain (Table 1).

**Table 1 Tab1:** Location of point set

Point name	Location
The upper point of the medial collateral ligament	A lateral tubercle located at the medial condyle of the femur
The lower point of the medial collateral ligament	The posterior part of the liriodendron area located at the medial condyle of the tibia
The upper point of the lateral collateral ligament	A lateral tubercle locating at the lateral condyle of the femur
The lower point of the lateral collateral ligament	The apex of the capitula fibula
The subpatellar ligament points	The lower part of the patellar ligament
The upper point of patella	Directly above the patellar bottom and located in the deep surface of the quadriceps tendon
The insertion of popliteal muscle	Located behind the upper part of the medial tibia
The medial popliteal fossa stimulation points	Located at the medial wall of the popliteal triangle, between the semitendinosus and semimembranosus’ muscles

After standard disinfection, the physicians will operate a Hanzhang type I no. 4 straight needle-knife (Beijing Huaxia Needle Knife Medical Equipment Factory) to perform acupotomy (Fig. 2). Physicians selected will have more than 5 years of experience and will be retrained for 16 h before the study begins.

**Fig. 2 Fig2:**
[figure not shown]
Needle-knife

The incision line will be consistent with the longitudinal axis of the lower limb. The body of the needle-knife will be perpendicular to the skin. The doctor will operate according to the following procedural steps: point fixation, orientation, pressure application, and penetration. When the needle-knife reaches the target depth, the doctor will perform a manual operation. The details of the manual operation are presented in Additional file 2. After the operation, the needle-knife will be pulled out, and local hemostasis will be applied for 3 min. The wound will be disinfected with iodine and dressed with a band aid. Patients will receive 2 acupotomy sessions for 2 weeks (once a week).

#### Sham acupotomy group

Patients assigned to the sham acupotomy group will receive mock acupotomy, which is performed similar to real acupotomy, but without manual stimulation to achieve any real effect. The needle-knife will pierce through the skin only and remain under the skin for 10 s to simulate the manipulation time. Patients will receive 2 sessions of sham acupotomy for 2 weeks (once a week).

Clinicians would give patients indomethacin cream (import drug registration number: H20181060, Nipro Pharma Corporation Saitama Site Plant 2) if the acupotomy treatment is not effective. All patients could receive up to one time of indomethacin cream per day. They can only receive indomethacin cream at most twelve times during the study. The researchers will record the use of indomethacin every day.

### Outcome measurement

We selected both clinical outcomes and surrogate outcomes to assess the efficacy of acupotomy. All outcomes will be measured at baseline and 1 week after the end of treatment. In addition, we will follow-up with patients to evaluate the WOMAC and VAS score at 3 and 6 months after the end of treatment (Table 2). Before the study begins, we will train the related investigators.

**Table 2 Tab2:** Study schedule. T1-T3: from the first treatment period to the third treatment period. W7: 1 week after the end of treatment. M3: 3 months after the end of treatment. M6: 6 months after the end of treatment

Study schedule						
Period	Screening	Baseline	Treatment	End	Follow-up	
Time	W-1	W0	W1-W6	W7	M3	M6
**Basic**						
Eligibility	√					
Demography	√					
Physical examination	√					
Medical history	√					
Informed consent	√					
**Outcomes**						
WOMAC		√		√	√	√
VAS		√		√	√	√
X-ray examination		√		√		
Musculoskeletal ultrasound imaging		√		√		
Plantar pressure measurement		√		√		
Maximum knee circumference		√		√		
Joint mobility		√		√		
**Trial evaluation**						
Informed consent	√					
Adverse event			√	√		
Safety evaluation			√	√		

### Primary outcome

#### WOMAC

The WOMAC is commonly used to assess KOA symptoms [20]. The scale includes 24 items in three parts, including 5 items related to pain, 2 items related to stiffness, and 17 items related to joint function. The scores are determined using a 10-cm-long visual analog scale beginning with 0 points and ending with 10 points. A score of 0 points indicates no symptoms for that item, and a score of 10 points indicates the most serious degree of symptoms for the item.

### Secondary outcomes

#### VAS score

The VAS score is commonly used to reflect the degree of bodily pain [21]. A 10-cm-long VAS scale beginning with 0 points and ending with 10 points will be used. A score of 0 indicates no pain, and a score of 10 indicate the most severe pain, which is intolerable.

